### Halting rules criteria

Any volunteer with G6PD deficiency who experiences grade 3 hemolysis following PQ administration will be discontinued from the use of PQ and monitored closely. If more than three subjects with G6PD deficiency are found to have grade 3 hemolysis following treatment with PQ for anti-relapse therapy, further treatment with PQ will be suspended for all G6PD-deficient subjects enrolled in the study.

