## Methods/design

### Study design

We are conducting a two-arm, cluster-randomized, open-label controlled trial of MMP with t3-day DHA-PIP and weekly PQ compared to focused screening and treating (FSAT) following current national treatment guidelines. Participants in the MMP arm receive a monthly 3-day course of fixed-combination tablet containing 40 mg of dihydroartemisinin and 320 mg of piperaquine phosphate for three consecutive months. Those aged 13 years and older receive low-dose weekly PQ (22.5 mg) therapy to prevent malaria transmission for 12 weeks. Participants in the FSAT arm are screened with highly sensitive polymerase chain reaction (PCR) methods, and all those testing positive for malaria receive therapy with first-line antimalarials following current national treatment guidelines. At the time of protocol development, artesunate-mefloquine combination therapy is the first-line treatment for *P. falciparum* in provinces with known antimalarial resistance, with a single, low dose of PQ (15 mg) to prevent malaria transmission. For participants in the FSAT arm with *Plasmodium vivax* malaria, the recommended treatment for asexual parasitemia is DHA-PIP. All patients with *P. vivax* in the FSAT arm receive treatment with 15 mg of PQ daily for 14 days if G6PD normal, or 45 mg weekly if G6PD deficient.

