### Treatment intervention

Volunteers randomized to MMP arm aged 13 years and older receive a monthly 3-day treatment course of (DHA-PIP; 360/2880 mg) for 3 months. They will also receive a weekly dose of 22.5 mg of PQ for 12 weeks. Children of 12 years of age or less will receive only a monthly 3-day weight-based treatment dose of DP for 3 months without PQ treatment. In the MMP arm, symptomatic patients or microscopy-confirmed parasitemia in the first 3 months are considered a failure of prophylaxis and treatment is given according to the national treatment guidelines. If the volunteer has parasitemia detectable by PCR only and is symptom free at monthly follow-up, the study treatment with monthly DHA-PIP is continued for 3 months as outlined for the MMP arm. To reduce phlebotomy requirements for G6PD testing and potential hemolytic risk in children, PQ is not be administered to those less than 13 years old.

Volunteers randomized to the focused screening and treatment (FSAT) arm are treated according to current national malaria treatment guidelines if they test positive for malaria based on blood smear and/or real-time PCR results during monthly follow-up. In the FSAT arm, all volunteers with parasitemia detectable with PCR receive antimalarial treatment, even if they are symptom- free.

At the time of protocol development, national treatment guidelines for areas of known piperaquine resistance, to include the designated study regions, recommended a 3-day course of artesunate and mefloquine (A + M) and a single 15-mg dose of PQ for acute *P. falciparum*, or DP for blood-stage *P. vivax* infection. Elimination interventions are carried out monthly during the first 3 months after enrollment, and then followed by 3 months of additional malaria assessment by smear and PCR diagnosis with malaria treatment as necessary following current national treatment guidelines (Fig. 1, Table 2, Fig. 2). Those febrile but negative for malaria are referred for evaluation and treatment of alternative diagnoses.

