**Fig. 1 Fig1:**
[figure not shown]
Study flow diagram

**Table 2 Tab2:** Table of times and events for adults and children over 12 years of age

Event	Screen/enroll day 1	Day 3^3^	Day 30^7^	Day 60^7^	Day 90^7^	Day 120^7^	Day 150^7^	Day 180^7^	Malaria diagnosis/ recurrence^2^
a. Informed consent	X								
b. Medical history	X								
c. Physical exam	X								X
d. Brief clinical evaluation and vital signs^1^			X	X	X	X	X	X	X
e. Malaria RDT, DBS, smear and PCR genotyping^6^	2 mL		1.5	1.5	1.5	1.5	1.5	1.5	1.5 mL
i. CBC	1 mL	1 mL^3^							
k. Molecular resistance markers^2^									6 mL
l. G6PD RDT, fluorescent spot, quantitative testing	1.5 mL								
m. Gametocyte PCR	2.5 mL		2.5	2.5	2.5	2.5	2.5	2.5	2.5 mL
n. Urine pregnancy test (women of child-bearing age)	X		X	X					X
o. Malaria treatment^4,5^	X		X	X					X
Daily phlebotomy (mL)	7	1^3^	4	4	4	4	4	4	10
Cumulative phlebotomy (approximately mL)	7		11	15	19	23	27	31	41

^1^Brief clinical evaluation includes an interval medical history, vital signs and a directed physical exam as indicated

^2^Performed only for volunteers with smear-positive malaria. Those with PCR-positive malaria will be treated following national guidelines but will not have blood drawn for molecular markers of resistance

^3^To be drawn for G6PD-deficient volunteers only. All G6PD-deficient volunteers with > 10% of Hgb or HTC drop on D3 will have CBC on day 7

^4^Patients screening positive on microscopy and/or PCR for *P. falciparum* malaria in the FSAT arm will receive currently recommended blood-stage antimalarials under published national treatment guidelines as well as single, low-dose primaquine (15 mg). Volunteers with *P. vivax* will be treated with the currently recommended blood-stage agent (DHA-PIP), as well as primaquine – G6PD-normal volunteers will receive 15 mg daily for 14 days, while G6PD-deficient volunteer will receive 45 mg × 8 weeks. All volunteers in the MMP arm will receive a fixed-dose 3-day course of DHA-piperaquine at 0, 24 and 48 h starting on days 1, 30, and 60, and a weekly 22.5-mg dose of primaquine for 12 weeks. All therapy will be directly observed

^5^For all volunteers with recurrent malaria, rescue therapy will be with the recommended agent(s) per national guidelines

^6^May be repeated as medically indicated (e.g., if patient is malaria-positive or otherwise ill on enrollment). An additional 0.5 mL will be collected on the day of enrollment for baseline G6PD genotyping

^7^Time window of ± 7 days

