### Comparison of MMP versus FSAT, and problems with the term “MDA”

The study is effectively comparing a large-scale malaria prophylaxis approach using currently available interventions with a more systematic version of current public health efforts to identify and treat infected persons. The primary objective of this study is to directly compare the effectiveness of MMP with DHA-PIP and weekly PQ against an active screening and treatment strategy following the current national malaria treatment guidelines. In the province where the study was conducted at the time of study inception, these included artesunate and mefloquine combination treatment for all acutely infected persons with *P. falciparum* malaria and DHA-PIP for *P. vivax* malaria. While PQ use – either single-dose for *P. falciparum* transmission-blocking or 14-day anti-relapse therapy for *P. vivax* infections – is currently advocated by treatment guidelines, implementation has been limited and use officially restricted to facilities able to screen for G6PD deficiency, greatly limiting application outside controlled research studies. Perhaps more important is the question of which, if any of the drugs involved can be safely administered on a large scale, with minimal or no medical supervision. Such practice, termed “mass drug administration,” is often considered as a means to treat significant numbers of infected individuals in limited-resource settings [32]. Because this term can be misconstrued, we have termed the key study intervention “malaria prophylaxis” rather than “mass drug administration” – the purpose is not merely to eradicate malaria within the individual, but to protect all treated individuals and their compatriots, treated and untreated, from the collective threat of malaria transmission. While blood-stage agents, such as A + M and DHA-piperaquine, achieve the former, only PQ administration has been shown to treat mature gametocytes responsible for mosquito transmission [33].

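### The study-wide hemolysis trigger counts only events after anti-relapse primaquine, so it leaves out the single 15 mg *P. falciparum* dose and makes prophylaxis-arm events arguable

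*Protocol article*

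**What the plan says.** The Halting rules criteria contain two rules in consecutive sentences.

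- **Individual rule:** "Any volunteer with G6PD deficiency who experiences grade 3 hemolysis following PQ administration will be discontinued" from further PQ. No indication is named.
- **Study-wide rule:** "If more than three subjects with G6PD deficiency are found to have grade 3 hemolysis following treatment with PQ for anti-relapse therapy", then "further treatment with PQ will be suspended for all G6PD-deficient subjects enrolled in the study". The count is limited by indication; the action is not.

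Elsewhere the protocol article gives the purpose of each PQ regimen.

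- **Single 15 mg dose for *P. falciparum*.** Study design pairs the first-line blood-stage treatment "with a single, low dose of PQ (15 mg) to prevent malaria transmission". Table 2, footnote 4, repeats the dose.
- **Weekly PQ in the MMP arm.** Study design says: "Those aged 13 years and older receive low-dose weekly PQ (22.5 mg) therapy to prevent malaria transmission for 12 weeks". The primary objective (Aim and objectives) adds radical cure, and Table 1 adds presumptive anti-relapse therapy.
- ***P. vivax* treatment.** Table 2, footnote 4, gives G6PD-deficient volunteers 45 mg weekly for 8 weeks.

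The G6PD testing section allows all classes of deficiency to enroll.

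**The concern.** A study-wide halting rule protects participants who have not yet been harmed; the individual rule acts only on someone already affected. If a deficient volunteer has grade 3 hemolysis after the single 15 mg dose, that volunteer stops PQ but the study-wide count does not move. If the count stands at three and the next event occurs in the MMP arm, whether PQ is suspended depends on which section of the protocol is taken to define that arm's PQ. The article gives no reason for counting a narrower exposure than the one suspended.

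**Working it through.** The protocol gives no operating characteristic for this rule, so there is no figure to reproduce. The check compares texts and adds simple dose arithmetic.

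**1. Exposure counted against exposure acted on.** The individual rule covers any PQ. The study-wide count covers PQ given against relapse. The study-wide action covers all PQ in all deficient subjects. The count is the only one of the three with an indication limit. Two other safety provisions have none: the Table 1 safety endpoint (hemolytic events in PQ recipients over 13) and the day 3 blood count in Clinical procedures.

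**2. Is the single dose anti-relapse in the protocol's vocabulary?** No. Study design gives its purpose as preventing transmission. The Discussion section comparing MMP with focused screening and treatment (FSAT) contrasts the two uses of PQ: single-dose for *P. falciparum* "transmission-blocking or 14-day anti-relapse therapy for" *P. vivax*.

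**3. Can a deficient volunteer receive it?** As written, yes. Study design and Table 2, footnote 4, attach no G6PD condition to the single dose, although both set one for *P. vivax* treatment. The dose is also not confined to FSAT. In the MMP arm, symptomatic or smear-positive cases in the first 3 months "are considered a failure of prophylaxis and treatment is given according to the national treatment guidelines", and the Limitations section says the arm reverts to standard of care after week 12.

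**4. Is MMP weekly PQ anti-relapse?** Study design names transmission only. The primary objective says transmission-blocking and radical curative. Table 1 says presumptive anti-relapse and transmission-blocking. Most of the text supports counting these events, but the halting rule does not say so.

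**5. Regimens open to a deficient volunteer aged 13 or older.**

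| Regimen | Total PQ | Individual rule | Study-wide trigger |
|---|---|---|---|
| *P. vivax* treatment | 45 mg × 8 = 360 mg | covered | counted |
| MMP weekly PQ | 22.5 mg × 12 = 270 mg | covered | probably counted, arguable |
| *P. falciparum* single dose | 15 mg × 1 = 15 mg | covered | not counted |

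The individual rule covers three of three. The trigger clearly counts one, leaves one arguable and omits one. The omitted dose is 15/360 = 1/24 of the first total and 15/270 = 1/18 of the second.

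**6. Illustration only, on assumed inputs.** The trigger needs at least 4 counted events, so P(trigger) = P(X ≥ 4) with X ~ Binomial(n, p). Only the arm size has a source: about 1000 people allocated 1:1, hence 500 per arm, all taken as PQ-eligible. The rest is assumed: 15% deficient, 30% of FSAT infected, half of those with *P. falciparum*, and p = 0.05 for every regimen. Then 500 × 0.15 = 75 deficient per arm, and 75 × 0.30 = 22.5, taken as 22 infected in FSAT, 11 of each species.

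- All PQ counts: n = 75 + 11 + 11 = 97, P = 0.72.
- Single dose left out: n = 75 + 11 = 86, P = 0.63.
- MMP weekly PQ left out as well: n = 11, P = 0.002.

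Across deficiency of 10–20%, FSAT infection of 10–50%, a *P. falciparum* share of 30–50% and p of 0.02–0.10, the first two probabilities each run from 0.02 to above 0.99. Leaving out the single dose lowers P by at most about 0.13 within a scenario. With both left out, the range is 0.00 to 0.47. The inputs are too uncertain to give a size, but they show that the MMP reading matters far more than the single-dose omission.

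**The case against.** The case for leaving the rule alone has real content.

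- **MMP weekly PQ is anti-relapse by the protocol's own account.** Table 1 uses that term, the primary objective calls the drug radical curative, and the Discussion on primaquine says the dose was informed by an earlier study of 22.5 mg weekly to prevent *P. vivax* relapse. This stands as far as intent goes: the events are probably meant to count, and the 0.002 above describes a reading that Table 1 contradicts. It does not remove the ambiguity, because the rule rests on an indication that Study design leaves out for this regimen.
- **The limit may be deliberate.** The Table 1 safety objective compares weekly PQ over 12 and 8 weeks, the two repeated regimens. That is possible, but the article states no such intent, and the action suspends all PQ, including the single dose.
- **MMP cases given the single dose have usually already had weekly PQ.** Their hemolysis may therefore count anyway. This largely stands; the clear gap is deficient FSAT volunteers with *P. falciparum* and no weekly PQ behind them.
- **Deficient patients may not receive the single dose under the national guidelines, which are not shown.** This cannot be excluded. As written, the article gives the dose without a G6PD condition.
- **The equal 5% rate in the illustration probably overstates the single-dose effect.** This stands, and the conclusion does not use it.
- **Individual safeguards apply to all PQ.** This is true and limits the harm. They do not do the study-wide rule's work, however, and Table 2 schedules routine blood counts only at enrollment and day 3, not through 12 weeks of dosing.

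**Conclusion.** The concern holds as a cheap improvement. Read literally, the study-wide trigger omits grade 3 hemolysis after the single 15 mg dose, and its wording leaves MMP weekly PQ events arguable although they are probably meant to count. The omission rests on the protocol's own terms and on the lack of any stated G6PD condition for the single dose. The practical effect is limited: the regimen clearly left out is the smallest exposure, and individual stopping plus the day 3 blood count (day 7 if the drop exceeds 10%) protect deficient volunteers under either reading. No probability is claimed, because the documents give no G6PD prevalence, hemolysis rate or species split.

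**What to change.** In the study-wide rule, drop the indication and use the exposure wording of the sentence before it, so that the condition counts more than three G6PD-deficient subjects with grade 3 hemolysis *following PQ administration in either arm*. Leave the threshold and the consequence ("further treatment with PQ will be suspended for all G6PD-deficient subjects enrolled in the study") unchanged.

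The cost is a one-phrase amendment, with no added visit or test. The downside is that the rule may be reached slightly sooner, which is acceptable for a safety rule.

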### Data storage and handling

Clinical and laboratory data pertaining to drug efficacy are collected and managed by AFRIMS Immunology and Medicine staff and RCAF personnel. All data and medical information obtained from study volunteers are considered privileged and confidential. Volunteers enrolling in the study are issued a unique identification code (UIC), which is used on all study files and clinical sample labels. Individually identifiable volunteer information other than the UIC are not transcribed on other study documents to include laboratory sample labels, case report forms, nor included in the presentation of study results. Data is double-entered into a Microsoft Access database (Microsoft Corp) with source data verification for each entry.

### Ethical approval

This trial has been approved by the Walter Reed Army Institute of Research (WRAIR) and the National Ethical Committee for Health Research (NECHR) in Cambodia.

## Discussion

### Overall rationale for the study

Elimination of malaria in mobile and migrant populations in border areas is of increasing importance as these transient populations carry a significant amount of MDR malaria burden in the GMS [8, 29, 30]. Despite the apparent urgency and attention to defining Southeast Asian mobile and migrant populations [31], the key operational elements of proposed malaria elimination strategies in these groups have yet to be rigorously tested in a well-controlled clinical study. This operational study protocol aims to define the most effective and reproducible components of a malaria elimination program specifically among Cambodian military forces. While the choice of approach and clinical regimen are important and oft-debated, the underlying premise of the present study is that the active engagement of military forces is likely to have a far reaching impact on overall elimination efforts. The sheer size, reach, and logistical capabilities of military forces leave them ideally suited to conduct large-scale elimination campaigns [11]. In that sense, the study also serves as a real-life training exercise for Cambodia’s military forces to develop needed capacities to manage malaria elimination efforts. The challenges of conducting a well-controlled elimination study are the same as those of conducting malaria elimination itself. Activities must be carefully coordinated by health workers trained in the use of exacting standard operating procedures and documented flawlessly. Functioning laboratories capable of maintaining high-quality control standards must be established. Much like military campaigns, these intensive efforts must be sustained for months or years. On all of these counts, the present study serves as the ideal training ground to build capacity and the skilled workforce that will be needed for Cambodia to scale up rigorous elimination efforts.

### Challenges in malaria elimination

While terms describing “mobile populations” are often used in reference to malaria elimination, they remain poorly defined, and encompass a wide range of persons including economic migrants, ethnic minorities, military and other government personnel, and tourists. Mobility among malaria endemic areas is their common shared trait, and for the most part, their mobility makes them more difficult to study. In this regard, military and government personnel may be the easiest of these varied groups to study because of the ability to provide comprehensive malaria prevention and treatment services reliably despite frequent movement. Military organization and chain of command provide frequent opportunities for structured intervention, suggesting that militaries may be among the easiest mobile groups to achieve early malaria elimination. Despite these advantages, the need to preserve operational and information security and the need to ensure that research does not interfere with the imperatives of military service remain important barriers. The Military is also considered a vulnerable population for medical research, and additional steps must be taken to ensure that study participation is never coerced through the chain of command. Potential transmission between surrounding communities and frequent personnel movements are additional challenges in designing interventions and assessing results [11].

### Comparison of MMP versus FSAT, and problems with the term “MDA”

The study is effectively comparing a large-scale malaria prophylaxis approach using currently available interventions with a more systematic version of current public health efforts to identify and treat infected persons. The primary objective of this study is to directly compare the effectiveness of MMP with DHA-PIP and weekly PQ against an active screening and treatment strategy following the current national malaria treatment guidelines. In the province where the study was conducted at the time of study inception, these included artesunate and mefloquine combination treatment for all acutely infected persons with *P. falciparum* malaria and DHA-PIP for *P. vivax* malaria. While PQ use – either single-dose for *P. falciparum* transmission-blocking or 14-day anti-relapse therapy for *P. vivax* infections – is currently advocated by treatment guidelines, implementation has been limited and use officially restricted to facilities able to screen for G6PD deficiency, greatly limiting application outside controlled research studies. Perhaps more important is the question of which, if any of the drugs involved can be safely administered on a large scale, with minimal or no medical supervision. Such practice, termed “mass drug administration,” is often considered as a means to treat significant numbers of infected individuals in limited-resource settings [32]. Because this term can be misconstrued, we have termed the key study intervention “malaria prophylaxis” rather than “mass drug administration” – the purpose is not merely to eradicate malaria within the individual, but to protect all treated individuals and their compatriots, treated and untreated, from the collective threat of malaria transmission. While blood-stage agents, such as A + M and DHA-piperaquine, achieve the former, only PQ administration has been shown to treat mature gametocytes responsible for mosquito transmission [33].

### Selection of safe, effective prophylaxis from a dearth of options

Selection of appropriate chemoprophylaxis requires a safe, tolerable, and effective drug that can be administered widely in the population. Such options, limited to begin with, are rapidly dwindling in the GMS as MDR malaria continues to gain a greater foothold [6]. The investigators selected DHA-PIP despite recent reports of declining treatment efficacy [3], though this was by no means a straightforward decision. Factors favoring its use included prophylaxis studies demonstrating efficacy of monthly administration of full DHA-PIP treatment courses in settings of known MDR malaria [34–36]. DHA-PIP remains inexpensive and very well-tolerated with an excellent safety profile, making it an ideal candidate for widespread administration [37, 38]. QT-interval prolongation is a known effect of piperaquine administration, though the clinical significance remains unclear, and limited data suggests reduced risk with a standard 3-day course of therapy [39]. Atovaquone-proguanil was also considered, but given its expense, daily administration and potential for rapidly developing resistance, the requirement for directly observed therapy (DOT) and strict follow-up would be difficult to scale up. Furthermore, mathematical modeling suggests that atovaquone-proguanil for MDA would result in further spread of resistance with only temporary returns in elimination of malaria [40]. Lastly, a newer ACT, pyronaridine-artesunate has been found to be well-tolerated and non-inferior to artemether-lumenfantrine and artesunate-mefloquine, but limited safety data precludes its use for an elimination campaign [41–43]. Though far from ideal, DHA-piperaquine was selected as the *least* unfavorable of currently available options in order to make current progress toward elimination rather than await alternatives. Though its efficacy has plummeted below accepted thresholds for treatment of acute *P. falciparum* infection, it is likely to retain efficacy against subclinical *P. falciparum* encountered in pre-elimination settings, and *P. vivax* infections [2, 3, 13, 44].

